### Recruitment

Participants were recruited using widespread efforts and multiple strategies throughout the Twin Cities, Minneapolis and Saint Paul, Minnesota, United States (Table 1). Targeted neighborhoods were identified, and canvassing efforts were carried out in these neighborhoods. Strategies for recruiting participants included attending local health fairs, staff informational sessions, and flyers posted throughout the community. Our primary sources of recruitment were word of mouth (snowball or respondent-driven sampling) and fliers.

The project logo was created by a local community artist and was used on promotional materials. In addition, a wide variety of community services were utilized for recruitment efforts. A partnership was also formed with a local community of churches to assist in church-based recruitment efforts.

**Table 1 table1:** Community-based recruitment source.

Sources of recruitment		Method
Weekly tabloid newspaper, monthly recovery newsletter, papers, African American community		Posted advertisements
Friend, family passed along study information		Provided fliers to participants, encouraged to share
**Health care**		
	Local clinics targeted for uninsured and underserved populations	Posted fliers, closed circuit television advertisements
	Utilization of community partnership with local clinic (medical, mental, and dental services)	Posted fliers, closed circuit television advertisements, service presentation to educate staffed facilitators
Apartment buildings, grocery stores, convenience stores, nail salons, office buildings, bus stations, liquor stores, coffee shops, community hot spots		Posted fliers around the metropolitan area
Community food shelves, Salvation Army		Placed fliers in bags given to consumers
Community centers, women’s resource centers, neighborhood organizations, adoption agency, participation in community events (eg, national night out, health fairs), affiliation with community organizations, Minneapolis Parks		Posted fliers, tabled at hosted events
American Indian Center, Division of Indian Work, American Indian Opportunities Industrialization Center, Minneapolis American Indian Center, Native Community Clinic		Enlisted assistance of member of the community for outreach, posted fliers
Fliers posted in elevators on University of Minnesota campus, campus dental clinic, tobacco research program hotlines		Posted fliers
Employment counselor/agency, workforce centers		Posted fliers
Treatment facilities/centers, detox, transitional housing		Posted fliers
**Education**		
	Child care centers, day care facilities, schools	In service presentations for staff, tabled at parent events
	Head start programs	Tabled at events, placed fliers in child’s bag for taking home
**Media**		
	Facebook, internet, television, Craigslist	Posted advertisements
	Radio	Participated in two radio interviews and ran a public service announcement on a local channel
Church, church group		Partnered with church organization of 12 local churches, provided in-service assistance, paid organization to assist with recruitment
Case worker/manager, child protection worker, public health nurse, nursing agency, Women, Infants and Children clinics, community facilitators		In-service presentations to educate about project to share with clients, posted fliers at agencies

### Participants

Prior to participant enrollment, all study procedures were approved by the Institutional Review Board. Participants called a designated study phone line to be screened for eligibility. All eligibility assessments were conducted over the phone, and initial eligibility status was determined immediately upon completion of the assessment.

A total of 195 participants were enrolled in this study (Figure 2). Recruitment occurred over 21 months, from June 2011 to March 2013. Final follow-up assessments were completed in August 2013. Participants were randomized to either biomarker feedback (active, n=98) or health education (control, n=97) conditions. Eligible participants were female. Although we initially allowed for enrollment of male parents/guardians, we discovered that our counselor did not feel comfortable conducting home visits with a male participant. Participants were at least 18 years of age, not planning to move out of the state over the next 3 months, willing to complete three assessments in their home over a 26-week study period, and the legal guardian of a child aged ≤10 years who lives in the home on at least 5 days of the week. In order to increase the likelihood that the home environment and the child’s urine assay would contain detectible tobacco toxins, participants were eligible if they endorsed smoking cigarettes on ≥20 days in the past 30 days, although they did not have to endorse smoking in the home. Participants were ineligible if they were pregnant, currently using any tobacco cessation aid (eg, counseling or NRT), homeless, living in a shelter or detox facility, living outside of a 30-mile radius of the university, or enrolled in a tobacco research study in the preceding 30-day period.

To determine positive smoking status, participants were asked to provide a urine sample at the baseline visit, which was tested using a NicAlert (Nymox Pharmaceutical Corporation, Quebec, Canada) test strip (a semiquantitative determination of cotinine levels in urine). Individuals with cotinine levels of >10 ng/mL on the NicAlert were verified as active smokers and eligible for study participation. In addition, the child enrolled needed to provide a minimum of 17 mL of urine for sample analysis of nicotine, cotinine, and NNAL. These laboratory assay results were required to provide biomarker feedback to participants in the active condition. If a sufficient amount of urine was not collected at the baseline visit, multiple attempts were made for additional collection visits. The participant was marked ineligible for participation if a sample was not collected from the child within a 2-week window of the baseline visit.

Further, home smoking was verified using a nicotine dosimeter placed in the participant’s home at the baseline visit for a total of 7 days. Upon successful retrieval of the dosimeter, a participant was considered eligible for study participation if their dosimeter value was greater than the limit of detection. The limit of detection for this study was 0.02 μg/m^3^ [42].

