### Outcomes

#### Primary and Secondary Outcomes

The primary outcome for this study is change in home SHS exposure measured by the passive air nicotine dosimeter at 26 weeks poststudy enrollment. The specificity of the nicotine dosimeter as a marker of SHS is an appropriate marker to measure a reduction in home air nicotine. Reduction in child’s cotinine and NNAL levels and parental report of smoking behavior change (ie, cessation, quit attempts, reduction, and restrictions) served as secondary outcomes. Specifically, carbon monoxide–verified, 7-day, self-reported point-prevalence abstinence assessed 6 months after study enrollment and defined as no smoking, not even a puff, for 7 consecutive days prior to the final assessment point at month 6 served as the smoking cessation measure [47]. Using a conservative approach, participants who dropped out or were lost to follow-up were considered to be smoking. Adoption of home smoking restrictions was assessed by a question modified from the Current Population Survey Tobacco Use Supplement [48]: “Which statement best describes the rules about smoking in your home?” Participants reported whether there were no bans (“Smoking is permitted anywhere”), some restriction (”Smoking is allowed in some places or at some times”), or complete restriction or ban (“No one is allowed to smoke anywhere”). Smokers were also asked to report the number of cigarettes smoked per day and the number of quit attempts in at least 24 hours since enrollment and their use of programs (eg, Helpline) or pharmacological therapy (eg, nicotine replacement therapy and other cessation medications) at weeks 8 and 26.

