#### Treatment Effect Moderators/Mediators

In order to examine psychological mediators and moderators of the proposed intervention (exploratory aims), key factors related to important determinants of smoking behavior change were selected for each set of analyses. These included proposed moderators of effect including sociodemographic variables for parent and child, baseline smoking, and social environmental variables. Participants were asked to detail the number of days they smoked in the last 30 days, the number of cigarettes they smoked on days they smoked, use of smokeless tobacco products and other tobacco used in the last 30 days, whether they used mentholated cigarettes, the number of 24-hour quit attempts they made in the past year, the longest time period they had without smoking a cigarette, and their lifetime nicotine replacement therapy use. Other tobacco-related variables included nicotine dependence, measured using “time to first cigarette” [49] and readiness to quit smoking [50]. Alcohol use [51] (ie, number of days one drank at least one drink, number of days one drank five or more drinks) was also assessed. Social environmental variables included the number of smokers living in the home, number of adult nonsmokers living in the home, outdoor smoking options, location where most smoking occurs, and adoption of home smoking restrictions in the home and car. Child exposure to tobacco smoke was also measured (ie, exposure to tobacco smoke in the home and outside the home in the past week). To assess any potential illnesses or health conditions that might impact the intervention or its effectiveness, parents were asked the following: “Has any health care provider ever told you that your child has any of the following illnesses: (eg, asthma, allergies, cancer, heart problems)?” Psychosocial variables included depressive symptoms (assessed using the 10-item Center for Epidemiological Studies Depression Scale [52]) and stress (measured using the 4-item Perceived Stress Scale [53]). Social influence was measured by asking how many of the participant’s five closest friends smoked cigarettes [54], and social support was measured via the Partner Interaction Questionnaire (Short-Form) [55]. Participants’ view of their social standing in the community and the nation was assessed using the MacArthur Scale of Subjective Social Status [56].

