#### Sample Size and Power Considerations

The sample size was chosen to ensure adequate power in order to examine the efficacy of tobacco-specific biomarker feedback in terms of the difference of SHS home exposure (primary outcome) between the two treatment groups at week 26. The power calculation was based on two-sided, two-sample *t* test assuming a type I error of 0.05. A total sample size of 180 (90 per treatment group) was determined to achieve 85% power in order to detect an expected difference (between 1.15 [SD 1.58] μg/m^3^ for the biomarker feedback group and 1.89 [SD 1.68] μg/m^3^ for the health education group) in air nicotine levels measured by dosimeters, which was derived from the assumed adoption rates of home smoking bans of the two treatment groups (55% vs 25%).

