### Statistical Analysis

#### Primary Analyses

For the continuous end points such as reduction (ie, change score) in SHS home exposure (primary outcome), child urinary cotinine levels (secondary outcome), and parental self-report amount of smoking, the primary analysis will be the two-sided *t* tests for the measurements at week 26. In case the distribution of nicotine or cotinine level shows nonnormality, the logarithm transformation on the biomarkers or nonparametric Wilcoxon rank sum test will be applied. Categorical variables such as the adoption of home smoking restriction policies and parental quitting behaviors will be analyzed using a Chi-square test (or the Fisher exact test if there are cells with a frequency ≤ 5).

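### Homes that already ban smoking can enroll and count as week-26 'adopters', because the restriction endpoint ignores baseline restriction status

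*Protocol article*

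**What the plan says.** Under Participants, mothers must have smoked on at least 20 of the past 30 days, "although they did not have to endorse smoking in the home". No criterion concerns the home's smoking rules. A second condition is environmental: "home smoking was verified using a nicotine dosimeter placed in the participant’s home at the baseline visit for a total of 7 days", and "a participant was considered eligible for study participation if their dosimeter value was greater than the limit of detection". The article adds: "The limit of detection for this study was 0.02" μg/m³.

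Under Primary and Secondary Outcomes, "Adoption of home smoking restrictions was assessed by a question modified from the Current Population Survey Tobacco Use Supplement". The item has three levels (no ban, partial restriction, complete ban) and asks about the rules now in force. It is not defined as a move from no ban to a ban.

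Under Primary Analyses, "Categorical variables such as the adoption of home smoking restriction policies and parental quitting behaviors will be analyzed using a Chi-square test", with Fisher's exact test for small cells. Restriction status is collected: Treatment Effect Moderators/Mediators lists "adoption of home smoking restrictions in the home and car" among the social environmental variables proposed as moderators. Covariate-adjusted regressions and mixed models appear only as supportive work under Secondary Analyses, where baseline restriction is not named.

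Sample Size and Power Considerations gives 85% power for a two-sided t test on air nicotine, with 90 per arm and means of 1.15 (SD 1.58) and 1.89 (SD 1.68) μg/m³. The difference is said to derive from ban adoption rates of 55% and 25%.

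**The concern.** A home that already has a complete ban cannot adopt one. If it enrolls and keeps its rule, it is still scored as a success at week 26 in whichever arm it falls. Such homes add the same expected number of successes to both arms, which pulls the two proportions together and inflates both. A reader would then take the reported percentage as an effect on behavior when part of it was there at entry.

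The body of the article treats restriction as secondary, but the abstract makes dosimeter-verified complete restriction the primary outcome, so the definition matters. The same homes may also have little room to fall on the air-nicotine change score. The variable needed to deal with this is already collected, yet it plays no part in the planned test.

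**Working it through.** **1. The plan's own power figure.** Difference 1.89 − 1.15 = 0.74. SE = √(1.58²/90 + 1.68²/90) = 0.243. Noncentrality 0.74/0.243 = 3.04. Two-sided power at 0.05 is 85.7%. The stated 85% reproduces.

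**2. What the inputs imply for a ban home.** Let b and n be the mean air nicotine in homes with and without a ban, and read the arm means as mixtures:

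- 0.55b + 0.45n = 1.15
- 0.25b + 0.75n = 1.89

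Subtracting gives 0.30(n − b) = 0.74, so n − b = 2.467. Hence b = 0.04 and n = 2.51. Moving each mean by ±0.005 for rounding puts b between 0.02 and 0.06. Within-group SDs of about 0 (ban) and 1.50 (no ban) give mixture SDs of 1.59 and 1.68, against 1.58 and 1.68 stated, so the mixture reading fits. The entry threshold of 0.02 therefore lies at or below the mean the plan itself implies for a ban home.

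**3. Dilution if 55% and 25% are conversion rates.** Let q be the share of enrolled homes with a complete ban at entry. The documents do not give q, so a range is assumed. Assume also that every baseline ban persists to week 26 and that these homes sit at the implied ban-home mean. Week-26 proportions are then q + (1 − q)×0.55 and q + (1 − q)×0.25, the risk difference is (1 − q)×0.30, and the nicotine difference is (1 − q)×0.74.

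| q | Week-26 proportions | Risk difference | Nicotine difference | t-test power, 90/arm | Chi-square power, all homes, 98 vs 97 | Chi-square power, homes without baseline ban |
|---|---|---|---|---|---|---|
| 0 | 55% vs 25% | 30 points | 0.74 | 86% | 99% | 99% |
| 10% | 59.5% vs 32.5% | 27 | 0.67 | 78% | 97% | 99% |
| 20% | 64% vs 40% | 24 | 0.59 | 70% | 92% | 97% |
| 30% | 68.5% vs 47.5% | 21 | 0.52 | 61% | 85% | 96% |
| 40% | 73% vs 55% | 18 | 0.44 | 52% | 75% | 92% |

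The t-test column is a Welch test with SDs from the mixture. For q = 20% the SDs are 1.487 and 1.676, SE = √((1.487² + 1.676²)/90) = 0.236, noncentrality 0.592/0.236 = 2.51, power 70%. Keeping the stated SDs instead gives 78%, 68%, 56% and 44% for q = 10% to 40%.

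The chi-square columns use Φ[(|p₁ − p₂| − 1.96 s₀)/s₁], with s₀ the pooled and s₁ the unpooled standard error. For q = 10%: s₀ = 0.0714, s₁ = 0.0687, (0.27 − 0.140)/0.0687 = 1.89, power 97%. The last column puts 98(1 − q) and 97(1 − q) homes into the same formula at 55% vs 25%.

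**4. If 55% and 25% are week-26 prevalences.** The contrast, and so the 85%, does not change. With persistent baseline bans the implied conversion rates are (0.55 − q)/(1 − q) and (0.25 − q)/(1 − q): 50% vs 16.7% at q = 10%, 43.8% vs 6.3% at q = 20%, and 40% vs 0% at q = 25%. The word adoption would then be the wrong label for the planning rates.

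**The case against.** The strongest case against runs as follows. An unadjusted chi-square is valid under randomization, with no bias between arms and no inflation of type I error. The dosimeter gate was meant to verify home smoking. The Background says that few low-income homes strictly enforce restrictions, so the baseline ban share may be small. The restriction test has power to spare: 98.8% at 55% vs 25% with 90 per arm. The supportive regressions, the mixed models over three time points and the moderator tests could all use baseline restriction.

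Most of this stands as a limit on the size of the problem. It does not remove the problem: the supportive and exploratory models leave the planned test as it is, and none of them defines adoption relative to baseline.

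Two stronger readings are tempting and are not supported:

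- A reader might infer that the 85% power is wrong, or holds only if no enrolled home had a ban. The figure reproduces. It falls only if the two rates are conversion rates in homes without a ban and baseline bans persist, and the size of the fall depends on a share that is not given.
- A reader might infer that homes with a working ban generally pass the gate and cannot improve. The back-solved mean has a rounding range that reaches the threshold, so it shows only that the gate cannot be relied on. Enrolled homes that report a ban are selected for detectable nicotine. Some may have poorly enforced bans with room to fall, and the documents give no level for them. The abstract's dosimeter verification might also remove some of them from the successes, but no cutoff is stated.

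**Conclusion.** The point holds in a limited form. Enrollment does not exclude homes that report a complete ban and have detectable nicotine, and the endpoint as worded counts them as adoptions in either arm. The consequence is dilution and a misstated adoption rate, not bias.

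Under the conversion-rate reading with persistent bans, an assumed baseline share of 10% to 30% costs 3 to 9 points of risk difference. It takes the chi-square test from about 99% to 97–85% power and the air-nicotine t test from about 85% to 78–61%. Restricting to homes without a ban keeps the chi-square at 96% or more over that range. Under the prevalence reading the stated 85% is untouched, and what remains is the label and the interpretation. The article does not settle which reading applies.

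**What to change.** - Make the main analysis of week-26 complete restriction a logistic model with arm and baseline restriction status (none, partial, complete). If nearly all baseline bans persist, the coefficient for that level may not be estimable; a penalized fit or a test stratified by baseline status serves the same purpose.
- Report adoption only among homes without a complete ban at baseline. The subset is fixed before randomization, so it introduces no selection between arms. Report the baseline ban share by arm.
- Add baseline restriction status as a covariate in the air-nicotine model.
- State in the sample-size section whether 55% and 25% are conversion rates in homes without a ban or week-26 prevalences. The 85% need not be restated.

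The cost is small: changed analysis wording and a model on data already collected. The adoption rate will have a smaller denominator and will no longer describe all randomized homes, which is why the adjusted model on everyone should lead. Since the article says analyses are complete, any analysis added now should be labeled as such in the results report.

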**Figure 2 figure2:**
[figure not shown]
Screening and enrolment of study participants.

### Randomization Process

After final eligibility was determined, participants were randomized into one of two conditions: biomarker feedback or health education. A block randomization with blocks of size 4 was used to improve balance. The statistician generated the randomization numbers for the study using R [computer program] (version R 2.13.0. Austria, Vienna: R Core Development Team), which were imported into and allocated through the Research Electronic Data Capture (REDCap) database. After final eligibility was determined, the assessment staff contacted the project administrator from the participant’s home to ask for the randomization assignment.

### Outcome Assessment Visits

Assessment visits at baseline, week 16, and week 26 were scheduled at the convenience of the participant and were conducted by community health workers at the participant’s home. Visits lasted between 60 and 90 minutes. Staff administered all surveys aloud in an interview format.

Study data were collected via an iPad using a secure, Web-based data collection instrument (REDCap) [43]. At the baseline visit, staff reviewed health education brochures with each participant in a one-time education session. The brochures provided information to participants about the risks of exposure to both SHS and THS, strategies for managing parenting stress, and tips to assist in quitting smoking. A number of additional activities took place at each assessment visit and are detailed below.

#### Urine Collection

Staff collected a urine sample from the youngest potty-trained child in the home. If no children in the home were potty-trained, a urine collection kit was provided to the parent for sample collection. The kit included two all-natural cotton pads, gloves, specimen bags, and an instruction sheet. Participants were instructed to wear gloves to prevent contaminating the sample with nicotine on their hands and to place a pad in the child’s diaper until it was urine soaked. Participants were encouraged to collect a sample overnight, the night before the scheduled visit for heavy soaking, and collect an additional sample the day of the visit. The pad was collected during the visit and transported to our offices where the urine-soaked pad was cut into 0.5-inch wide strips using scissors and placed in a syringe. The syringe was used to extract the urine from the soaked pad. The urine was expelled into a bio specimen cup and stored in a –80°C freezer until it was sent to the laboratory for assaying.

If the identified child was potty-trained, parent assistance was requested to place a specimen commode (aka “hat”) in the toilet for collection and to assist the child in sample collection. Each urine sample was analyzed for the presence of nicotine, a nicotine metabolite (cotinine), and NNAL.

#### Nicotine Dosimeter

At each assessment visit, staff hung a passive air nicotine dosimeter [31], which is an objective, validated method to quantify the level of ambient nicotine present in the air. The dosimeters consist of a filter treated with sodium bisulfate and contained in a 4-cm polystyrene cassette. Nicotine passively diffuses to the dosimeter and binds to the filter. The nicotine dosimeter was hung in the main activity room of each home, as well as the family car, if available. The dosimeter remained in the home and car for a minimum of 7 days for sample collection. After 7 days, staff collected and shipped the dosimeter to the University of California, Berkeley, for analysis using gas chromatography to quantify the presence of nicotine in the air.

